# Efficacy and safety of fire needle therapy for blood stasis syndrome of plaque psoriasis: protocol for a randomized, single-blind, multicenter clinical trial

**DOI:** 10.1186/s13063-020-04691-7

**Published:** 2020-08-25

**Keywords:** Fire needle therapy, Plaque psoriasis, Blood stasis syndrome, Randomized controlled trial, Study protocol

## Abstract

**Background:**

Fire needle therapy is a characteristic treatment in traditional Chinese medicine (TCM). An increasing number of studies have indicated that fire needle treatment for psoriasis provides satisfactory results with few side effects and a low recurrence rate. We herein describe the protocol for a multicenter, randomized, single-blind, placebo-controlled trial that will provide high-quality evidence on the efficacy and safety of fire needle therapy for plaque psoriasis.

**Methods:**

Ninety-two patients with blood stasis syndrome (BSS) of plaque psoriasis will be enrolled and randomly assigned to receive fire needle therapy (intervention group) or fire needle control therapy (control group) once a week for 4 weeks. The Psoriasis Area and Severity Index (PASI) score will serve as the major efficacy index, while the body surface area (BSA), Physician Global Assessment (PGA) score, Dermatology Life Quality Index (DLQI) score, patient-reported quality of life (PRQoL), visual analog scale (VAS) score for itching, TCM symptom score, and relapse rate will be assessed as secondary outcomes. The PASI score, BSA, PGA score, and VAS score for itching will be evaluated at baseline and during the 4-week treatment and follow-up periods. DLQI score, PRQoL, and TCM symptom score will be assessed at baseline and during the treatment period. Recurrence will be evaluated during the follow-up period. Safety assessments include vital sign monitoring, routine blood tests, blood biochemistry, routine urine tests, pregnancy tests, physical examinations, and adverse-event recording. SAS software will be used for data analysis. The data network platform will be designed by the data management center of Nanjing Ningqi Medical Technology Co., Ltd.

**Discussion:**

It is believed that fire needle therapy can activate the meridians, promote blood circulation, and regulate skin immunity. BSS of plaque psoriasis is related to not only immune dysfunction but also poor or stagnant blood flow. We anticipate that the results of the trial described in this protocol will provide strong evidence for the safety and efficacy of fire needle therapy for BSS of plaque psoriasis.

**Trial registration:**

Clinicaltrials.govNCT03953885. Registered on May 15, 2019. Name: Fire Needle Therapy on Plaque Psoriasis with Blood Stasis Syndrome

## Background

Psoriasis is a chronic inflammatory skin disease characterized by red papules or plaques covered with silvery-white scales [1]. The pathogenesis is unclear but believed to involve interactions among genetic factors, the immune system, and the external environment [1, 2]. The global prevalence of this condition varies from 0.51 to 11.43% in adults and 0 to 1.37% in children [3]. In China, the prevalence is approximately 0.47% [4]. Current treatments primarily involve the use of biological agents such as T cell inhibitors, tumor necrosis factor-alpha (TNFα) inhibitors, interleukin (IL)-12/23 blockade, and other targeted therapies [1]. However, these targeted therapies are expensive and not effective in all cases. Consequently, the majority of patients resort to traditional Chinese medicine (TCM) therapy.

TCM is known for its unique theoretical system. TCM doctors use individualized treatments after syndrome differentiation in each case; these may include Chinese herbal medicine, acupuncture, and moving cupping therapy [5], among others. Fire needle therapy, a characteristic TCM therapy, is a form of acupuncture treatment. It involves the penetration of needles heated over alcohol lamps at the designated acupoints on the human body; based on TCM theory, this warms yang and expels cold, disperses stasis and relieves pain, and warms and activates the meridians [6]. In the clinical setting, fire needle therapy has proven effective for some diseases, such as moderate-severe acne [7] and nodular prurigo [8]. According to TCM theory, blood stasis syndrome (BSS), one of the basic syndromes of psoriasis, is caused by poor or stagnant blood flow [9]. A previous study showed that fire needle therapy is effective for plaque psoriasis in the stationary phase with few side effects and a low recurrence rate [10]. Similarly, a growing body of evidence has shown satisfactory clinical efficacy of fire needle therapy for plaque psoriasis [11]. However, to our knowledge, there is a dearth of multicenter, blinded studies using only fire needles and emollients for the treatment of psoriasis.

We herein present the protocol for a multicenter, randomized, single-blind, placebo-controlled trial for objective and standardized evaluations of the clinical efficacy and safety of fire needle therapy for plaque psoriasis. The aim of the trial is to obtain objective evidence in accordance with international standards and aid in the development of clinical norms that will facilitate the treatment’s popularization and clinical application.

## Methods/design

### Study setting

This is a multicenter, single-blind, randomized controlled trial to investigate the efficacy and safety of fire needle therapy for plaque psoriasis. The study will be performed in five centers in China: Yueyang Hospital of Integrated Traditional Chinese and Western Medicine, Shaanxi Hospital of Traditional Chinese Medicine, First Affiliated Hospital of Heilongjiang University of Traditional Chinese Medicine, Affiliated Hospital of Jiangxi University of Traditional Chinese Medicine, and Traditional Chinese Medicine Hospital of Shijiazhuang. Participants will be assigned to treatment and control groups using a centralized randomization system (implemented by a data network platform designed by Nanjing Ningqi Medical Technology Co., Ltd.). The detailed process is shown in a flowchart in Fig. 1.

**Fig. 1 Fig1:**
[figure not shown]
Study flowchart. This is the protocol for a randomized controlled trial on the efficacy and safety of fire needle therapy for blood stasis syndrome of plaque psoriasis

This protocol has been developed according to the Standard Protocol Items: Recommendations for Interventional Trials (SPIRIT) 2013 guidelines [12]. This checklist is described in detail in Additional file 1. The protocol has been approved by the institutional review board (IRB) of Yueyang Hospital of Integrated Traditional Chinese and Western Medicine, Shanghai University of TCM (ethical approval number: 2019–033), and the study is registered at *clinicaltrials.gov* (ID: NCT03953885; registration date: May 15, 2019).

### Diagnostic criteria

In Western medicine, the diagnostic criteria for plaque psoriasis have been formulated in accordance with *Guideline for the diagnosis and treatment of psoriasis in China (2018 simplified edition)* [13], whereas those for BSS of plaque psoriasis have been drafted according to the *Evidence-based clinical practice guide for psoriasis vulgaris* by the Dermatology Branch of China Association of Chinese Medicine [14].

Accordingly, participants will be diagnosed with plaque psoriasis based on the following criteria [13]: First, the skin lesions appear as dark red plaques or invasive erythema with clear boundaries showing white or silvery-white scales. Second, features such as the “wax drop phenomenon,” “film phenomenon,” “point bleeding phenomenon” (Auspitz sign), and “bundle hair” can be found during physical examination. Third, the scalp, back, and extremities are the most susceptible areas for skin lesions. Fourth, itching may or may not be present. Fifth, the Koebner phenomenon can be observed in the advanced stage. Finally, the skin lesions are prone to relapse, with the majority alleviated in summer and aggravated in winter.

The main sign of BSS of plaque psoriasis is the prolonged presence of dark red, hypertrophic, infiltrating skin lesions. Minor signs include scaly dry skin, a soot-black facial complexion, cyanosis of the lips and nails, dark menstrual blood or blood clots in female patients, a dark purple tongue with ecchymosis and/or petechiae, an unsmooth pulse, and a thready/moderate pulse. The presence of BSS will be confirmed when patients show the main sign along with more than one minor sign [14, 15].

### Inclusion and exclusion criteria

Participants will be recruited from five hospitals in China: Shaanxi Hospital of Traditional Chinese Medicine, Yueyang Hospital of Integrated Traditional Chinese and Western Medicine, First Affiliated Hospital of Heilongjiang University of Traditional Chinese Medicine, Affiliated Hospital of Jiangxi University of Traditional Chinese Medicine, and Traditional Chinese Medicine Hospital of Shijiazhuang. Each research center has one or two clinical research observers (CRO) who will explain this trial to participants before they voluntarily sign an informed consent form at the beginning of the study. On the consent form, participants will be asked if they agree to the use of their data, should they choose to withdraw from the trial. Participants will also be asked to grant permission for the research team to share relevant data with the universities taking part in the research or regulatory authorities, where relevant. This trial does not involve the collection of biological specimens for storage.

The general inclusion criteria for the study are as follows: (1) compliance with the abovementioned diagnostic criteria for plaque psoriasis and BSS of plaque psoriasis; (2) skin lesions involving ≤ 10% of the body surface area (BSA), with primary involvement of the trunk and/or limbs, palms/soles, and/or face/scalp (vulva not included); (3) aged 18 to 65 years (inclusive of 18 and 65 years); and (4) provision of written informed consent for participation in the study.

Exclusion criteria will be applied as follows: (1) presence of other progressive skin diseases that may affect assessment of the condition; (2) treatment with the research drugs, biological agents, and immunosuppressive agents within 1 month before study initiation; (3) treatment with topical glucocorticoids and/or phototherapy within 2 weeks before study initiation; (4) presence of severe, uncontrolled, local or systemic, acute or chronic infection; (5) presence of severe systemic diseases, elevation of alanine aminotransferase or aspartate aminotransferase levels by > 1.5 times the upper limit of normal, elevation of creatinine by 1.5 times the upper limit of normal, decrease in any main blood test parameters (white blood cell count, red blood cell count, hemoglobin amount, platelet count) to below the lower limit of normal, or abnormalities in other laboratory test parameters; (6) history of malignant neoplasms, primary or secondary immune deficiency, and/or a hypersensitivity reaction; (7) major surgery within 8 weeks before study initiation or scheduled during the study period; (8) pregnancy or lactation; (9) history of alcohol abuse or drug abuse, family history of cancer, personal or family history of a serious mental illness; (10) any other factors considered by the researchers as contraindications for study participation.

Criteria for trial suspension, patient rejection, and patient withdrawal are also set as follows: (1) development of other serious or life-threatening organic lesions during the trial, (2) withdrawal at the individual’s discretion, (3) poor patient adherence to treatment, (4) participation in another trial administering treatment that may interfere with the results of the present study, (5) refusal to take contraceptive measures during the trial period (including both treatment and follow-up periods), (6) loss to follow-up for various reasons, and (7) incorrect application of the inclusion and exclusion criteria.

### Randomization and masking

This trial will follow a randomized, single-blind design. The data management company will use a centralized randomization system to generate random codes, which will be sent to the project lead unit. The project lead unit will prepare a random code table and distribute it to the participating units. The random code will then be distributed to the participants by the CRO of each participating unit. Only the CRO responsible for patient recruitment will be aware of the group allocation until the participants have completed the trial. All other research staff, including the individual responsible for measurements, will remain blinded to the group allocation. If participants know which group they belong to, they will be instructed to refrain from sharing the information with the individual responsible for measurements. The participants will be informed of their results only after completion of recruitment, interventions, and evaluations for all participants.

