### Data confidentiality and management

With the exception of the CRO responsible for the participants, participants’ information will be kept confidential from research staff until publication of the study results. All of their documents related to this trial, such as CRFs, will be represented by the participant’s unique random code. Random codes and CRFs will be sealed and stored in a separate filing cabinet. To facilitate data analysis, CRO will also use a unified data collection system for recording (established by Nanjing Ningqi Medical Technology Co., Ltd. Data Management Center, Nanjing, China). The results of this trial will be published in an international peer-reviewed journal.

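### Allocation concealment is not secured as written: a random code table goes to the sites, and the recruiting CRO knows the allocation

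*Protocol article*

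**What the plan says.** All references are to the protocol article.

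- **Study setting:** "Participants will be assigned to treatment and control groups using a centralized randomization system".
- **Randomization and masking, generation:** "The data management company will use a centralized randomization system to generate random codes, which will be sent to the project lead unit".
- **Same section, distribution:** "The project lead unit will prepare a random code table and distribute it to the participating units". Then: "The random code will then be distributed to the participants by the CRO of each participating unit".
- **Same section, knowledge of allocation:** "Only the CRO responsible for patient recruitment will be aware of the group allocation until the participants have completed the trial". All remaining research staff, among them the person who takes the measurements, are said to stay blinded.
- **Inclusion and exclusion criteria:** each centre has "one or two clinical research observers (CRO) who will explain this trial to participants before they voluntarily sign an informed consent form". Exclusion criterion 10 is open-ended and rests on the researchers' judgement.
- **Table 2:** the inclusion and exclusion criteria are marked at screening and again at week 0. Randomization is also marked at week 0.
- **Fire needle group and Fire needle control group:** the operator heats the needle in one arm and not in the other.
- **Data confidentiality and management:** random codes and case report forms are sealed and kept in a separate cabinet. The responsible CRO is exempt from the rule that keeps participant information from research staff.

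**The concern.** Concealment means that whoever decides on a patient's entry cannot know or guess the next assignment until that decision is final. Generating the sequence centrally does not achieve this if a table of the sequence then sits at the site. Here the table goes to the site, the site CRO hands out the codes, and the recruiting CRO is the person named as knowing the groups. Entry also leaves room for judgement: blood stasis syndrome is diagnosed from signs such as complexion, tongue and pulse, and exclusion 10 is discretionary.

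A recruiter who could see what comes next could admit, defer or exclude patients accordingly, even without intending to. The arms would then differ in prognosis for reasons unrelated to treatment. Adjustment can remove only the part of such a difference that runs through measured covariates. The article expects the trial to supply a high level of evidence, and that depends on this step.

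A second fault in the same section concerns masking, not concealment. The operator cannot be among the blinded staff, because the operator must know whether to heat the needle.

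**Working it through.** **1. Can the recruiter foresee assignments?** The plan gives no figure on this point, so the check is to set the sections side by side.

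| Question | What the article says | What it leaves open |
|---|---|---|
| Who generates the sequence? | The data management company, by a central system | – |
| Where does it go? | To the project lead unit, then as a table to the sites | Whether the table shows groups or bare codes |
| Who gives out codes? | The CRO at each site | Whether this is the CRO who recruits, where a site has two |
| Who knows the group? | The CRO responsible for recruitment | Whether before or only after each assignment |
| Is eligibility settled beforehand? | It is checked at week 0, the randomization visit | The order of steps within that visit |
| Is each assignment released singly after a lock? | Not described | – |

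No row closes the route from the table to the recruiter. Study setting speaks of central assignment, but the section that sets out the procedure uses the central system only to generate codes. The two accounts need to be reconciled.

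**2. Illustration of the stakes.** The size of any selection effect is an assumption; the article gives none.

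Inputs:
- n = 47 per group (Sample size section; the centre totals in Table 3 are 20 + 20 + 18 + 18 + 18 = 94)
- two-sided α = 0.05 (same section)
- assumed shift δ = 0.1 to 0.3 SD in the compared outcome, with no true treatment effect

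Formulas:
- non-centrality λ = δ√(n/2), with √(47/2) = 4.848
- rejection rate = 1 − Φ(1.96 − λ) + Φ(−1.96 − λ)

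| δ (SD) | λ | Upper tail | Lower tail | Type I error |
|---|---|---|---|---|
| 0 | 0 | 0.025 | 0.025 | 0.050 |
| 0.1 | 0.485 | 0.070 | 0.007 | 0.077 |
| 0.2 | 0.970 | 0.161 | 0.002 | 0.163 |
| 0.3 | 1.454 | 0.307 | 0.000 | 0.307 |

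With 38 per group, the number before the dropout allowance, √(38/2) = 4.359. The three shifted rows then become 0.072, 0.141 and 0.258.

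**3. The same illustration on the response-rate scale.** Take no true effect, response rates centred on the 35.3% control rate from the Sample size section, and a normal-approximation test of two proportions. An assumed selection-induced difference then gives these type I errors:

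| Difference | 38 per group | 47 per group |
|---|---|---|
| 5 points | 7.4% | 8.0% |
| 10 points | 14.8% | 17.2% |
| 20 points | 44.5% | 52.8% |

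Both scales show that a small imbalance already takes the error above 5%, and that the size depends wholly on the assumed shift.

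**4. Masking.** If all staff other than the recruiting CRO are blinded, so is the operator. The two intervention sections make that impossible. This contradiction needs no arithmetic.

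**The case against.** The strongest reply is that the article never says the recruiter sees an assignment in advance. The table may hold bare codes, since trial documents are identified by each participant's random code. Knowing the allocation while the trial runs is also compatible with learning it only once a patient has been assigned. Study setting does speak of assignment through the central system, and random codes are said to be sealed. This stands as a limit on what can be claimed. It does not restore concealment: no step prevents foreknowledge, and the sealing is described as record storage, not as envelopes opened after enrolment.

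Four stronger readings are tempting and are not supported:

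- **That all 94 allocations are foreseeable.** Label content and timing are unstated. Table 3 splits the 94 into 18 to 20 per centre, so nothing suggests that one recruiter sees them all.
- **That one person takes consent, recruits, hands out codes and records data.** The article says "Each research center has one or two clinical research observers (CRO) who will explain this trial to participants" before the form is signed. It does not say that they take the signature, and where there are two the duties may be divided.
- **That outcome data are biased at entry.** The article does say "CRO will also use a unified data collection system for recording", but it names a separate, blinded person for measurements and does not say that the CRO scores PASI.
- **That the type I error is 16% to 31%.** This needs a shift of 0.2 to 0.3 SD, for which the article gives no basis. At 0.1 SD the figure is about 8%.

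The illustration also carries the shift in full into the compared outcome. The primary outcome is a decrease in PASI, and adjustment for confounders is planned. Either could absorb part of a measured imbalance, but neither removes an unmeasured one.

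**Conclusion.** The point holds in limited form. The stated procedure does not secure allocation concealment, and it conflicts with the central assignment described under Study setting. This is not detail left to a fuller document, because the article sets out the weak procedure explicitly. What is shown is that the recruiter may be able to foresee assignments. A reader might infer that allocation was in fact foreseen or that selection took place; the text supports neither.

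The documents do not allow the size to be estimated. Under the assumed shift of 0.1 to 0.3 SD with 47 per arm, a nominal 5% test would reject a true null in about 8% to 31% of trials. With 38 per arm the range is about 7% to 26%. These figures show sensitivity and are not a forecast.

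The statement that all other staff stay blinded is wrong for the operator and should be corrected, as a separate matter of masking.

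**What to change.** 1. Delete the step that sends a code table to the sites, and keep the list only inside the central system already contracted.
2. Release assignments one at a time, and only after consent, eligibility and baseline PASI have been recorded irrevocably. Release each to the treating operator and not to the recruiting CRO.
3. Align Study setting with Randomization and masking so that both describe this one procedure.
4. State that the operator is necessarily unblinded and neither scores nor enters outcomes.
5. In the trial report, disclose how allocations made before the change were released: what the table showed, who held it, and when the CRO learned each assignment.

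The cost is a change of access rights in the existing system, a log-in per patient by the operator, and an amendment, which the Quality assurance system section says each centre's review board must approve. Its reach is limited. Recruitment began in June 2019 and is due to end in December 2020, and the article is dated August 2020, so the change protects only the remaining enrolment. For patients already enrolled, disclosure is the available remedy.

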### Interventions

Patients will be randomly assigned to receive fire needle therapy (intervention group) or fire needle control therapy (control group) once a week for 4 weeks. In addition, all patients will receive basic treatment, including prescription of a moisturizing lotion, instructions to avoid inducing and aggravating factors, instructions to bathe appropriately, and lifestyle recommendations.

#### Fire needle group

The participants in this group will wear eye masks and fully expose the lesions. After selecting the acupoints, the operator will routinely disinfect his/her hands and the acupuncture points on the participants. Then, the operator will select an acupuncture needle measuring 0.4 × 40 mm, ignite the alcohol lamp, and continuously move the needle from its root to its tip in the outer flame until the needle turns red; this is for disinfection of the needle. After disinfection, the operator will heat the needle tip and body in the outer flame until it turns completely red (the length of the red portion is determined by the acupuncture depth) and rapidly penetrate the skin lesion in a vertical direction; the depth of the acupuncture is based on the thickness of the skin lesion. Puncture will be performed from the lesion periphery to the lesion center at intervals of 0.3 to 0.5 cm.

